## 1. Relevance to the call for proposals:

The health effect of alcohol consumption pattern (moderate and binge drinking) is of significant public health relevance because alcohol consumption in Norway and other countries in Northern Europe have been increasing since 2000. Furthermore, the consumption pattern is changing from binge drinking towards moderate regular intake. Norway is in a fortunate position to address this issue because large scale health surveys with data on both moderate and binge drinking have been linked to a multigenerational database, hospital discharge on CVD morbidity and mortality and other registries.

The national policy building upon a premise that total consumption affects number of problem drinkers might be under pressure. An implication of this principle of solidarity is that anyone can potentially experience health problems due to alcohol consumption. However, the scientific evidence base for population wide approaches is challenged for several reasons:

First, the effect of alcohol consumption on CVD appears to be divergent (RQ 1). But also, alcohol consumption might be influenced by underlying factors, which calls for a reconsidering on the issue of human agency in policy formulation. Individual and personal characteristics, such as psychosocial and cognitive, might explain a large and increasing part of the variation in health behavior (RQ 2). It has also been suggested that personal characteristics to an increasing extent explain socioeconomic inequalities in health. A better understanding of vulnerable subgroups in modern society where according to social theorists, the individual is put at an increased responsibility for managing their own health risk, is imperative for developing future health and alcohol policy. And finally, both alcohol consumption and CVD risk tend to be clustered within families (RQ 3&4). This could indicate the scope for early prevention of both harmful alcohol use and CVD.

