### **Approaches, hypothesis and choice of method**

The study has some important strengths: the sample size and comprehensive data linkage, the availability of information on both moderate and binge drinking, reasonably long follow-up and linkage to information on both morbidity and mortality. Using morbidity data on hospital discharge on incidences of CVD increases the number of cases by a factor of approximately three to four compared to mortality data, and further increases statistical power further (RQ 1). This enables us to investigate combinations of moderate alcohol consumption and binge drinking. Having clinical endpoints in addition to mortality will be a significant improvement to the literature. It has been suggested that effects of binge drinking could be an artifact due to misclassification or have a non-atherosclerotic pathology.

The study will be able to look into more detail than has previously been possible on the long-term prognosis among patients with preexisting CVD or other high risk subgroups (RQ 1). In terms of drinking patterns, the results of individual level cohort studies mainly apply to cohorts who predominantly drink regularly with few heavy drinking occasions. Adequate power to investigate the combined effect of moderate and binge drinking requires large cohorts with enough data on the distribution of such drinking patterns within a population and information on exposure to other heart disease risk factors, pre-existing CVD as well as cognitive ability, mental distress and family data.

We will in this study be able to investigate if the abstainers might be a selected group more closely, and for a wider range of potential underlying factors, than has previously been done (RQ 2 and 3). An assessment on how these factors relate to alcohol consumption and heart disease will also broaden our understanding on the clinical and public health impact of alcohol in groups at particularly high risk (RQ1 and 2).

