## **Statistical methods**

Sample size and power: The materials used to address RQ 1 is considerably higher powered than those used in previous research. Power calculations have been conducted using the `sampsi` command in STATA and the program `Quanto` for interaction terms. RQ 1: Two options have been used: Either to report the effect of moderate alcohol consumption adjusted for binge drinking or to test formally for interaction between average alcohol consumption and reported binge drinking. We have calculated the last because we consider this the most conservative approach. The relative risk of main effects has for average alcohol consumption reported to be 0.75 and for binge drinking 1.45. If we assume that 10 % in the cohort develop CVD in the follow up period, power of 80 % and set p-value at 5 % for two sided tests, we would need a sample of 7,960 individuals, which is well below our sample of 55,876 individuals. RQ 2 and 3: Prevalence of mental distress in CONOR is on average 10 %, and the effect of depression on CVD is assumed to be 1.6. If we want to detect a 50 % difference in effect of binge between depressed and not depressed subjects, we would need 26,740 individuals (in our sample  $n=47,848$ ), and for frequency of alcohol use 53,680 individuals (in our sample  $n=162,048$ ). RQ 4: As we do not know the strength of association between alcohol consumption and sibling and parental CVD morbidity and mortality, it is difficult to calculate sample size exactly for this sub study. For this reason, we have preliminary investigated this issue, and found that it appears to be higher risk of CVD in fathers and same sexed sibling among those who are abstainers compared to those who drink moderately. The hazard ratio of CVD death in fathers among those who abstain from alcohol compared to moderate drinkers was 0.93 (0.88-0.99). RQ 5: It is not straightforward to estimate power in within sibling analyses. With a total of 5050 CVD endpoints, and based on our experiences in an analysis with similar design and number of endpoints, we consider it likely that we will be able to detect differences large enough to be theoretically interesting. RQ 6: With 3500 alcohol related cases, we consider it highly likely that we will be able to detect meaningful degree of familial aggregation for mental distress and CVD morbidity and mortality.

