Data analysis: For time to event outcomes such as morbidity and mortality the primary modelling strategy is to use Cox proportion hazard regression models. In RQ 1 the effect of moderate alcohol consumption will be analysed by adjusting for binge drinking and across strata of binge drinking (interaction term will be fitted to formally test if the effect differs). In RQ 2-3 the same strategy will be employed using strata of cognitive ability and mental health. In RQ 4 the aim is to see if using alcohol consumption among family members as instrumental variable will reproduce a protective effect of moderate alcohol consumption as seen in conventional analysis. Using instruments, it will also be possible to estimate the effect sizes and compare the effect and pattern in CONOR participants with that of their sibling. To achieve this, z-scores will be calculated based on units of alcohol consumption reported. For RQ 5, the effects of alcohol consumption will be estimated by comparison between siblings or co-twins ("fixed effect"). This approach effectively matches out all factors shared between siblings that may confound the effect of alcohol on cardiovascular mortality reported in studies of unrelated individuals. The analyses will be conducted in the statistical software STATA. Age, smoking status and number of cigarettes per day in smokers, physical activity, self-reported disease (CVD, diabetes, antihypertensive medication) and psychosocial distress at baseline will be adjusted for as potential confounders. In

familial aggregation analysis, we will estimate to what extent alcohol related mortality co-occur in first degree family members with CVD morbidity and mortality and mental distress by summing up number of family members with any of these traits.

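### Effect modification in RQ 1–3 is assessed only on the hazard-ratio scale, although the protocol also wants conclusions on public health impact in high-risk groups, which depend on excess or avoided cases

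*Protocol*

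**What the plan says.** Protocol, Statistical methods, Data analysis: for time-to-event outcomes "the primary modelling strategy is to use Cox proportion hazard regression models". In RQ 1 moderate drinking is analysed with adjustment for binge drinking and across binge strata, and an "interaction term will be fitted to formally test if the effect differs". For the next two questions, "In RQ 2-3 the same strategy will be employed using strata of cognitive ability and mental health". The product term and the stratum-specific estimates are both hazard ratios.

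Statistical methods, Sample size and power, works on the same scale. It gives these main effects: "The relative risk of main effects has for average alcohol consumption reported to be 0.75 and for binge drinking 1.45". For RQ 2 and 3, "the effect of depression on CVD is assumed to be 1.6", with a 10% prevalence of distress and a 50% difference in effect as the interaction to detect.

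On purpose, the section on relevance to the call seeks "A better understanding of vulnerable subgroups in modern society" as a basis for policy. The section on approaches and choice of method expects RQ 1 and 2 to inform "the clinical and public health impact of alcohol in groups at particularly high risk". The protocol mentions no risk difference, rate difference, absolute risk by stratum or RERI.

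**The concern.** In a Cox model, no interaction means equal hazard ratios. If two groups have different baseline risks, equal hazard ratios imply unequal numbers of extra (or avoided) cases per 1,000 people, and equal numbers imply unequal hazard ratios. The protocol itself assumes different baseline risks, since it gives distress a relative effect of 1.6.

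Public health impact in a high-risk group is a matter of how many cases drinking causes or averts there, and the planned outputs do not give that directly. If the product term were the only evidence on effect modification, a null result could accompany a clearly larger burden in the distressed. A ratio below 1 could accompany an equal or somewhat larger one. In RQ 1, an unchanged absolute benefit among binge drinkers would look like weakened protection, which is the direction the protocol's background expects.

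**Working it through.** **Inputs, all from Sample size and power:** binge 1.45; moderate (average) consumption 0.75; distress 1.6, prevalence 10%; and "10 % in the cohort develop CVD in the follow up period, power of 80 % and set p-value at 5 % for two sided tests". The relative effects are treated as risk ratios. The reference group has neither factor, and its risk is set to 1.

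**The plan's own figure.** The 26,740 stated for the distress-by-binge interaction cannot be reproduced, because the binge prevalence and the direction of the 50% difference are not given. A Wald calculation for a Cox product term, with 10% CVD and 53.7% with any binge episode (100 − 46.3, from the CONOR binge item), gives 14,924 for a ratio of 1.5 and 17,870 for 1/1.5. The same formula reaches 26,740 at a binge prevalence of about 8% or 77% (ratio 1.5), or 18% or 77% (ratio 1/1.5). The figure is therefore not shown to be wrong, and nothing below depends on it.

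**RQ 2, binge by distress.** Excess from bingeing in the non-distressed = 1.45 − 1 = 0.45. Excess in the distressed = 1.6 × (1.45 × ratio − 1). RERI = RR11 − RR10 − RR01 + 1, which equals the difference between the two excesses.

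- No ratio interaction: excess in the distressed = 1.6 × 0.45 = 0.72, and 0.72/0.45 = 1.6. RERI = 2.32 − 1.45 − 1.6 + 1 = 0.27.
- Equal excess: HR in the distressed = (1.6 + 0.45)/1.6 = 1.281; Cox ratio = 1.281/1.45 = 0.884.

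| Cox ratio | HR in distressed | Excess in distressed | Relative to 0.45 | RERI |
|---|---|---|---|---|
| 0.884 | 1.281 | 0.45 | 1.00 | 0 |
| 0.90 | 1.305 | 0.488 | 1.08 | 0.038 |
| 0.95 | 1.378 | 0.604 | 1.34 | 0.154 |
| 1.00 | 1.450 | 0.72 | 1.60 | 0.27 |
| 1.50 | 2.175 | 1.88 | 4.18 | 1.43 |

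From 0.884 to 1.00 the two scales give different answers. Outside that range they agree in direction.

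**Per 1,000, no ratio interaction.** Reference risk = 0.10/[(1 + 0.45p)(1 + 0.6 × 0.10)], with p the binge prevalence (assumed, since the protocol gives none for this purpose).

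- p = 20%: 0.10/(1.09 × 1.06) = 0.0866. Excess 39 v 62 per 1,000.
- p = 53.7%: 0.10/(1.242 × 1.06) = 0.0760. Excess 34 v 55 per 1,000.

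**RQ 1, moderate drinking by binge.** Avoided risk without bingeing = 1 − 0.75 = 0.25. For the same avoided risk in binge drinkers, HR = (1.45 − 0.25)/1.45 = 0.828 and the Cox ratio = 0.828/0.75 = 1.10, which reads as attenuated protection. With no ratio interaction, the avoided risk in binge drinkers is 1.45 × 0.25 = 0.3625 and RERI = 1.0875 − 0.75 − 1.45 + 1 = −0.11.

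**Would a ratio of 0.884 be detected?** N for 80% power = (1.960 + 0.842)² × Σ(1/cell event probability)/ln(0.884)². At p = 20% the cell event probabilities are 0.0626, 0.0227, 0.0111 and 0.0036, the reciprocals sum to 430.4, ln(0.884)² = 0.0153, and N is about 220,600. At p = 53.7% N is about 176,200. Power at n = 47,848 = Φ(√(47,848/N) × 2.802 − 1.960):

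- p = 20%: Φ(0.466 × 2.802 − 1.960) = Φ(−0.655) = 26%.
- p = 53.7%: Φ(0.521 × 2.802 − 1.960) = Φ(−0.500) = 31%.

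**The case against.** The strongest reply is that nothing in the Data analysis paragraph is wrong. RQ 2 and 3 ask whether distress, cognition or socioeconomic position account for, or interact with, the alcohol effect, and a ratio-scale product term is a standard answer to that. The vulnerability and impact wording comes from the case for funding and the rationale, not from the research questions. A separate SAP could add absolute measures. Most of this stands: the Cox test should stay, and the point is an improvement and not a correction. It does not remove the mismatch, because the protocol itself fixes the scale and itself says that RQ 1 and 2 will inform impact in high-risk groups.

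A reader might be tempted by four stronger readings, which the protocol does not support.

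- *The plan would declare distressed people no more vulnerable, or less so.* The protocol has no rule that equates a null product term with no vulnerability. With equal excess, the low power makes a finding of no interaction the likelier report, and that is also the right additive answer.
- *A ratio of 0.88 would be read as protection.* The hazard ratio in the distressed is then 1.28, which is harm, and the planned stratum analysis would show it.
- *The same figures apply to pre-existing CVD.* The protocol plans to look at risk in that subgroup but specifies no product term and no baseline risk for it.
- *The additive scale should settle every statement on vulnerability.* That is debatable. The protocol's aims support it only for statements about impact or numbers of cases.

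Part of the RQ 1 hypothesis is also independent of scale. If protection is absent among substantial binge drinkers, HR = 1 and the risk difference is zero.

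**Conclusion.** The point holds as a limited mismatch between scale and purpose. On the protocol's own inputs, a null Cox interaction is compatible with 1.6 times the binge-related excess in the distressed (39 v 62 or 34 v 55 per 1,000, depending on the assumed binge prevalence), and equal excess appears as a ratio of 0.88. In RQ 1, equal absolute benefit appears as a ratio of 1.10.

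The distress-by-binge discordance is confined to ratios of about 0.88 to 1.00. At a 50% increase both scales point the same way, with about 4.2 times the excess.

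The result assumes that 1.45, 0.75 and 1.6 act as risk ratios, that 1.6 (given for depression) applies to the distressed group among those who do not binge, and that overall CVD risk is 10%. It does not show that the Cox test is wrong or that the stated sample sizes are wrong.

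**What to change.** Keep the Cox interaction as the test of relative effect modification. For RQ 1–3, prespecify from the same models:

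- joint exposure-by-stratum categories with one common reference group;
- RERI with a confidence interval;
- standardised absolute risk differences for drinking within each stratum, at a stated follow-up time.

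Add one sentence saying that statements on public health impact or excess cases rest on these absolute measures and not on the Cox product term alone, while statements on relative effect modification rest on the product term. Fixing this beforehand also prevents the scale from being chosen once results are known.

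The cost is a few lines of post-estimation in Stata and no new data. The downside is two scales to report and interpret, which may differ.

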## Research questions (RQ)

- (1) To investigate the risk and protective effects on CVD morbidity and mortality associated with various combinations of moderate alcohol consumption and binge drinking. We will here also look at risk in the sub-group of patients with pre-existing CVD.
- (2) To investigate if the effects of moderate alcohol consumption and binge drinking on CVD can be explained by or interact with mental distress (depression and/or anxiety).
- (3) To investigate if the effects of moderate alcohol consumption and binge drinking on CVD can be explained by or interact with cognitive ability (IQ), educational level, or other socioeconomic factors.
- (4) First, to investigate how alcohol consumption in family members are related to CVD risk among index individuals. Secondly, to use alcohol consumption among siblings and offspring as instrumental variable to assess the causal effects of alcohol consumption pattern on CVD.
- (5) Using pairs of siblings, monozygotic and dizygotic twins discordant for CVD to estimating the association between moderate alcohol and binge drinking and CVD within families. These results will adjust for early life and family factors.
- (6) To assess familial aggregation of mental distress, alcohol related mortality and CVD morbidity and mortality.

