## **2. Aspects relating to the research project**

### **Background and status of knowledge**

Alcohol has a negative effect on many health-related outcomes but for heart diseases the effects seem to be mixed. Alcohol use is negatively related to hypertensive disease, hemorrhagic stroke and atrial fibrillation. For ischemic heart disease (IHD) and ischemic stroke (cardiovascular diseases, CVD), the relationship is complex. Chronic heavy alcohol use has been associated with adverse cardiovascular outcomes. But light to moderate drinking seems to be related to reduced risk of ischemic diseases.

It is not well understood to what extent frequent episodes of heavy alcohol consumption may counteract the beneficial effect on heart disease and by which mechanisms episodes of heavy alcohol have a negative effect on heart disease. Even rare and occasional episodes of binge drinking seem to increase the risk in a recent study from the northernmost part of Norway. One would expect the protective effect to be more pronounced in individuals who do not binge drink, and not present in individuals who report substantial binge drinking. A recent meta-analysis on binge drinking including only 4718 IHD events gave some support for this notion. Our study will add to this by 6500 CVD cases.

Norwegian studies on adolescent and adult abstainers have shown higher risk of psychosocial factors and might suggest a J-shaped pattern. A general finding is that abstainers tend to have worse health and are poorer. One interpretation of this and similar findings is that since alcohol is such an important token in social interaction, abstainers are likely to differ as a social group and have a wide range of individual characteristics that could put them at increased risk of several health problems. Those who have moderate intake have in studies been shown to have higher cognitive ability compared to abstainers and that heavy drinkers have lower cognitive ability.

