### **Samples (sub-populations)**

#### **RQ 1:**

The CONOR and the NTR will be pooled together and the NTR will be used as a cohort for this purpose. This will include n=47,848 from CONOR and n=8028 individuals from NTR (n=55,876 in total) with complete data on both moderate and binge drinking. Mean year of birth is 1947 in CONOR and 1941 in the NTR sample. More deaths occur in the NTR (n=1453 deaths) compared to CONOR (n=1805 deaths). Number of CVD deaths in the CONOR sample with follow-up until 2010 is 547. Based on the proportion of CVD mortality and all-cause mortality and number of fatal and non-fatal cases in the FS-database, total

number of cases, including both CONOR and the NTR is expected to be 3000 IHD and 3500 cases of stroke.

RQs 2 and 3:

This will include the CONOR and twin populations linked to the FS-data on hospital discharges, the Cause of Death Registry, the Conscript Registry (cognitive ability) and Social Security Registry (mental health problems). Two separate sub-populations of CONOR will be studied: all subjects who responded to items on moderate alcohol consumption (n=162,048) and, nested in this sample, those who responded to items on both moderate and binge drinking (n=47,848). In the first group there are 3774 deaths from CVD. There are in total 9735 acute myocardial infarction and 8926 stroke incident cases from the FS-database in CONOR. For the second group, see RQ1.

RQ 4:

This issue will be analyzed in a linkage between CONOR, cardiovascular health surveys in the Norwegian Family Based Life course study and the FS-data on hospital discharges. There are 116,037 individuals in CONOR with information on parents and siblings. Of these, 109,800 individuals have responded on the moderate alcohol consumption question with 9729 CVD deaths in fathers and 31,050 on the binge drinking question with 1854 CVD deaths occurring after the year of CONOR examination.

RQ 5:

CONOR: There are 48,401 siblings in CONOR with the same mother and father. 1025 of these have by 2010 died (281 CVD). We expect approximately 1400 CVD endpoints in the FS-database. For the second group on siblings, see RQ 1.

RQ 6:

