**Binge drinking**

Questions in CONOR:

“Approximately how often during the past 12 months have you consumed alcohol corresponding to at least 5 glasses of liquor in 24 hours?”

In all 47,848 participants (26,151 men and 21,697 women), and answers varied from zero to 99 times during the last year. Nearly half (46.3%) reported zero, and the frequency was a higher in men than in women.

In NTR:

1990 questionnaire: “Approximately how many times during one year do you drink more than 5 bottles of beer, one bottle of red or white wine or a quarter bottle of liquor?” (Never, 1-4 times a year, 5-10 times a year, once a month, 2-3 times a month, once a week, 2-4 times a week or every day or almost every day?)

Life course socioeconomic position: Highest educational level, household income (yearly updated), Childhood parental occupational class and education, and housing conditions from Censuses 1960 onwards).

Cognitive ability/Intelligence in late adolescence: The Norwegian National Conscript Service examines more than 90% of the male population at age 18-19 years. General ability is a composite score based on 3 speeded subtests. The Arithmetic Test (25 minutes) has 30 items in prose and measures logical reasoning and arithmetic and algebraic ability; it is similar to the arithmetic test in the Wechsler Adult Intelligence Scale (WAIS). The Word Similarities Test (8 minutes) is a multiple-choice test with 54 items, akin to the vocabulary test in WAIS. The Figures Test (20 minutes) has 36 multiple-choice items with 6 or 8 alternatives and is similar to Raven’s Progressive Matrices.

The CONOR mental health index: This consists of summative index including seven questions on mental distress scored 1-4: “Have you, in the course of the last two weeks, felt: Nervous and unsettled? Troubled by anxiety? Secure and calm? Irritable? Happy and optimistic? Sad/depressed? Lonely?” Response categories are “No”, “A little”, “Quite a bit” and “Very”. This index captures a combination of symptoms of anxiety and depression. This index has been validated, has good internal consistency and correlates highly with the total score for Hospital Anxiety and Depression Scale (HADS) ( $r=0.76$ ) and with Hopkins symptom checklist (HSCL-10) ( $r=0.70$ ).

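### RQ 3 asks about education and other socioeconomic factors, but the stated analysis gives them no stratum, interaction term or place among the covariates

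*Protocol*

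**What the plan says.** Under Research questions, RQ 3 asks whether the effects of moderate and binge drinking on CVD "can be explained by or interact with cognitive ability (IQ), educational level, or other socioeconomic factors". It names three items, and asks of each whether it explains the effect or modifies it.

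The Main variables section makes the data available: "Life course socioeconomic position: Highest educational level, household income (yearly updated), Childhood parental occupational class and education, and housing conditions".

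Under Statistical methods, the Data analysis paragraph describes RQ 1 as Cox models for moderate drinking, adjusted for binge drinking and fitted across its strata, with an interaction test. It continues: "In RQ 2-3 the same strategy will be employed using strata of cognitive ability and mental health". The adjustment set is then listed: "Age, smoking status and number of cigarettes per day in smokers, physical activity, self-reported disease (CVD, diabetes, antihypertensive medication) and psychosocial distress at baseline".

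The Background says of the natural reference group: "A general finding is that abstainers tend to have worse health and are poorer".

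**The concern.** The question and the stated analysis do not match. A team following the Data analysis paragraph would finish RQ 3 with a result for cognitive ability and none for education or other socioeconomic factors, on either the explanation or the interaction side.

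The gap also reaches the main cohort estimates. The project's overall aim is to assess a possible protective effect of moderate drinking. If abstainers are poorer and poorer people have more CVD, leaving social position out makes moderate drinkers look better than they should. The protocol itself cites an educational gradient in CVD mortality. It also promises, for RQ 2 and 3, a closer look at whether abstainers are a selected group.

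**Working it through.** **Step 1. Set the text side by side.** The three items of RQ 3 were traced through Main variables and Statistical methods.

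| Item in RQ 3 | Listed as a variable | Stratum or interaction | In covariate list | Power statement |
|---|---|---|---|---|
| Cognitive ability | Yes (conscript data, men) | Yes | No | No |
| Educational level | Yes | No | No | No |
| Other socioeconomic factors | Yes (income, childhood position, housing) | No | No | No |

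Two of three items have no stated analysis. The power paragraph points the same way: for RQ 2 and 3 it gives 26,740 and 53,680 individuals, both for mental distress. The sample description for RQs 2 and 3 labels the Conscript Registry with cognitive ability and the Social Security Registry with mental health, and labels no source with education or income.

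**Step 2. Does another part of the plan fill the gap?**
- RQ 5 (sibling and co-twin fixed effects) removes what siblings share. It does not remove differences between siblings in their own education or income. In CONOR it uses 48,401 of 181,891 people (48,401/181,891 = 27%), plus the twin pairs. It leaves the RQ 1-3 hazard ratios unchanged and does not answer RQ 3.
- RQ 4 (family members' drinking as instrument) addresses mainly reverse causality and is a separate estimate.
- Cognitive ability cannot stand in. RQ 3 lists it as a separate item, and the conscript data cover men only.

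**Step 3. How large could the bias be?** The protocol gives neither education by drinking group nor its association with CVD, so every input here except 3,774 and 0.75 is an assumption. For one binary factor (low social position), with prevalence p_m in moderate drinkers and p_a in abstainers and CVD hazard ratio R given the planned covariates, a true null appears approximately as

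B = [1 + p_m(R − 1)] / [1 + p_a(R − 1)].

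For scale, ln 0.75 = −0.288, where 0.75 is the relative risk that the power paragraph cites for average consumption. With the 3,774 CVD deaths in the frequency sample and an assumed 30% abstainers, SE(log HR) ≈ 1/√(3774 × 0.3 × 0.7) = 0.0355.

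| R | p_m v p_a | B | ln B / ln 0.75 | ln B / SE |
|---|---|---|---|---|
| 1.2 | 30% v 40% | 1.06/1.08 = 0.981 | 6% | −0.5 |
| 1.2 | 25% v 45% | 1.05/1.09 = 0.963 | 13% | −1.1 |
| 1.5 | 30% v 40% | 1.15/1.20 = 0.958 | 15% | −1.2 |
| 1.5 | 25% v 45% | 1.125/1.225 = 0.918 | 30% | −2.4 |
| 2.0 | 30% v 40% | 1.30/1.40 = 0.929 | 26% | −2.1 |
| 2.0 | 25% v 45% | 1.25/1.45 = 0.862 | 52% | −4.2 |

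More extreme inputs go further: 20% v 50% with R = 2.0 gives 1.20/1.50 = 0.80. Because R is conditional on smoking, activity, disease and distress, which plausibly carry part of the social gradient, the upper rows deserve at least as much weight as the lower ones.

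**Step 4. What would adjustment cost in records?** Family linkage is stated to exceed 90% only for those born after 1940, and mean birth years are 1947 (CONOR) and 1941 (twins). Parent and sibling information exists for 116,037 of 181,891 CONOR participants (64%), and for 31,050 of 47,848 with binge data (65%). If childhood data follow that linkage, a model requiring them would lose about a third of records.

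**The case against.** The strongest reply is that the Data analysis paragraph is a summary. Its covariate list also omits sex, which suggests shorthand. RQ 3 commits the team to the question, the variables are listed, and an explanation-type question is often answered by starting from a model without the candidate factor. Exact model blocks may sit in an analysis plan that is not at hand.

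Part of this stands: it is not shown that the team will never fit such models. But the protocol does not leave the choice open. It names particular strata and particular confounders, and both lists pass over what RQ 3 names. That is a mismatch in text the protocol itself fixes.

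It is also fair that other designs deal with some social confounding. The protocol attributes a substantial part of the educational gradient to family factors shared by siblings, which RQ 5 removes. That helps the project as a whole, but not RQ 3 or the RQ 1-3 estimates.

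A reader might go further and infer that the protocol itself names social position as the likely explanation of the protective effect. It does not. Beside poverty, the Background mentions worse health and a broad set of individual characteristics, and the methods text raises reverse causality from unmeasured illness.

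**Conclusion.** The mismatch is established from the text and needs no assumed number: two of the three items in RQ 3 have no stated analysis, and the stated RQ 1-3 cohort models do not adjust for own education or income.

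The likely direction of the resulting bias is toward apparent protection. This rests on the protocol's remark that abstainers are poorer and on its educational gradient in CVD mortality.

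Its size is not known. A reader might infer from the table that much of a hazard ratio of 0.75 would be confounding by social position. The document does not support that: the range of 0.98 to 0.86 comes from assumed prevalences and hazard ratios, and the residual effect may be small once the planned covariates are in. What the table does show is that, with this many events, a modest residual bias could reach conventional significance under some of the inputs. The point is a worthwhile correction, not evidence that the planned estimates are wrong.

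**What to change.** In the Data analysis paragraph:

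1. Add educational level and household income to the strata and interaction terms for RQ 2-3.
2. Add highest education and household income in the baseline year to the covariates. Later yearly income values should not be used, since they can follow the exposure or the disease.
3. Report the RQ 1-3 hazard ratios for moderate and binge drinking with and without these two variables, on the same records. The comparison answers the explanation part of RQ 3, and the interaction terms answer the rest.
4. Where linked, adjust for childhood parental class and education and for housing in a further sensitivity model. It should not be the deciding model, because linkage may be incomplete for older participants.

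The cost is a change of wording, a few extra Cox models on variables the protocol already lists, and some records lost to missing education or income. Using the same records for both models keeps that loss from distorting the comparison between them.
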